## Abstract

Pulmonary rehabilitation (PR) constitutes a cornerstone of non-pharmacological management in chronic obstructive pulmonary disease (COPD); however, its clinical effectiveness is frequently attenuated by suboptimal patient adherence and the absence of individualized, continuous monitoring within the home setting. Internet of Things (IoT) technology offers a promising solution to these persistent challenges; however, comprehensive closed-loop management models that fully integrate IoT capabilities remain underexplored. This prospective, non-randomized controlled intervention study will enroll 588 patients with moderate-to-severe stable COPD (GOLD grades 2–4) from a single institution. Participants will be assigned to either conventional PR (Group A) or IoT-assisted PR (Group B) based on initial preference and technology readiness. Group B will receive IoT-enabled devices and a smartphone app to support home-based PR, including daily respiratory muscle training and structured aerobic/resistance exercise (3–5 sessions/week). Group A will receive standard PR education and guidance. Follow-ups will occur at weeks 4, 12, 26, and 52. The primary outcome is the 12-month rate of moderate-to-severe AECOPD. Secondary outcomes include pulmonary function, exercise capacity, HRQoL, right cardiac function, pneumonia incidence, all-cause mortality, and adherence. Analyses will be performed on an intention-to-treat basis. This study will evaluate the efficacy of an IoT-based pulmonary rehabilitation management model in reducing AECOPD-related readmissions and improving exercise tolerance, quality of life, and dyspnea in patients with moderate-to-severe COPD, while examining its feasibility and safety in a real-world setting. The findings may support the development of a technology-enabled continuous care model for chronic respiratory diseases, facilitating the transition from hospital-centric to patient-centric care and advancing the application of smart nursing and remote health management. The study protocol has been registered with the Chinese Clinical Trial Registry (ChiCTR2500106412).

## Introduction

1

Chronic obstructive pulmonary disease (COPD) is a common, preventable, and treatable condition characterized by persistent respiratory symptoms and airflow limitation, imposing a substantial and escalating burden on healthcare systems globally (1, 2). In China, the prevalence among adults aged 40 years and older has been reported at 13.7%, establishing COPD as a primary public health priority (1). The chronic and progressive nature of COPD, coupled with recurrent acute exacerbations (AECOPD), drives progressive declines in exercise capacity and health-related quality of life (HRQoL), as well as substantially increased healthcare costs (2).

Although pharmacological therapy remains indispensable, non-pharmacological interventions—particularly pulmonary rehabilitation—are equally critical for optimizing patient outcomes (1). Pulmonary rehabilitation (PR) is defined as a comprehensive, individualized intervention that includes exercise training, health education, and behavior modification (3). This intervention aims to improve the physical and psychological condition of individuals with chronic respiratory diseases and to promote sustained adherence to health-enhancing behaviors (4, 5). Robust evidence has confirmed that PR confers clinically meaningful improvements in dyspnea, exercise capacity, and quality of life in patients with COPD (6–9). Accordingly, the Global Initiative for Chronic Obstructive Lung Disease (GOLD) strongly recommends PR for patients with moderate-to-severe disease (10).

Despite the well-established efficacy of PR, its implementation in traditional home settings without remote clinician supervision often yields suboptimal adherence and clinical benefits due to lack of real-time monitoring and individualized feedback (11, 12). Patients frequently lack the knowledge, motivation, and ongoing support needed to maintain complex exercise regimens, leading to attenuated long-term benefits (13, 14). Key barriers include insufficient awareness of the importance of PR, absence of real-time professional guidance, and a lack of individualized, engaging rehabilitation programs. Accordingly, developing innovative, patient-centered models that enhance the accessibility, engagement, and personalization of home-based PR represents an urgent clinical need (11, 15).

Internet of Things (IoT) technology, enabling real-time data exchange between patients and healthcare providers through interconnected devices and platforms, represents a significant advancement in contemporary healthcare delivery (16). Although IoT has been explored for continuous vital sign monitoring in COPD management (17–20), existing evidence for PR is limited, especially for patients with moderate-to-severe COPD and a history of exacerbations. Most studies are characterized by small sample sizes and short follow-up periods, precluding robust assessment of long-term clinical outcomes. Moreover, substantial heterogeneity in intervention design has hindered the development of a standardized IoT-based PR management model (21).

In response to these gaps, the present study aims to conduct a prospective cohort investigation to develop and evaluate an IoT-based PR management model and to assess its impact on clinical outcomes in patients with moderate-to-severe COPD. The specific objectives are as follows: (1) to compare the effect of an IoT-assisted PR management model versus conventional care on the rate of AECOPD-related readmissions within 12 months post-discharge; (2) to evaluate the model’s efficacy in improving exercise tolerance, dyspnea, HRQoL, pulmonary function, and rehabilitation adherence; and (3) to examine the safety and feasibility of IoT-assisted PR management, thereby providing evidence-based support for clinical practice.

## Methods and analysis

2

### Study design

2.1

This is a prospective, pragmatic, non-randomized controlled intervention study with a 52-week follow-up period. The intervention is actively assigned based on patient preference and technology readiness, and the study includes a concurrent control group receiving standard care. The study protocol has been registered with the Chinese Clinical Trial Registry (ChiCTR2500106412). Study design and reporting will adhere to the Standard Protocol Items: Recommendations for Interventional Trials (SPIRIT) guidelines (22). Figure 1 is the trial flow chart.

**Figure 1 fig1:**
[figure not shown]
Flow chart of the study.

### Study setting and participants

2.2

Participants will be recruited from the Department of Respiratory and Critical Care Medicine, Shijiazhuang People’s Hospital, Shijiazhuang, Hebei Province, China.

#### Inclusion criteria

2.2.1

Age between 40 and 75 years.A confirmed diagnosis of COPD according to GOLD criteria, defined as a post-bronchodilator FEV₁/FVC ratio < 0.70 and FEV₁ % predicted < 80% (GOLD grades 2–4) at enrollment.A history of at least two moderate acute exacerbations or one severe acute exacerbation requiring hospitalization within the preceding 12 months (Group E according to the GOLD guideline).Clinical stability for a minimum of four weeks prior to enrollment, defined as the absence of acute exacerbations or changes in pharmacological regimen.Capacity to provide written informed consent and willingness to comply with all study procedures, including utilization of IoT devices and the smartphone application.

#### Exclusion criteria

2.2.2

Inability to participate in PR or operate IoT devices due to severe cognitive impairment, physical disability, or communication barriers.Presence of other significant respiratory comorbidities (e.g., active pulmonary tuberculosis, lung malignancy, or bronchiectasis as the primary diagnosis), unstable cardiac conditions (e.g., recent myocardial infarction), or other comorbidities that would preclude safe participation in PR.Current enrollment in another interventional clinical trial.Pregnancy or lactation.

#### Study withdrawal criteria

2.2.3

Participants meeting any of the following criteria will be withdrawn from the study following enrollment:

Development of a concurrent acute illness requiring intervention that would confound study outcomes.Failure to complete required assessments, rendering evaluation of the primary outcome impossible.Occurrence of a serious adverse event during follow-up that, in the investigator’s judgment, necessitates withdrawal from the trial.Pregnancy occurring during the follow-up period.Voluntary withdrawal, loss to follow-up, or death during the follow-up period.Post-enrollment discovery that the participant does not fulfill any inclusion criterion or meets any exclusion criterion.

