### Statistical analysis

3.4

Data will be analyzed using SPSS version 23.0 and R (version 4.2 or above). The following analytical approaches will be employed:

(1) Data description: continuous variables will be assessed for normality using appropriate statistical tests. Normally distributed data will be expressed as mean ± standard deviation (x̄ ± s); non-normally distributed data will be presented as median (interquartile range). Categorical variables will be summarized as frequencies (*n*) and proportions (%).(2) Between-group comparisons: categorical variables will be compared using the chi-square test or Fisher’s exact test, as appropriate. Normally distributed continuous variables will be analyzed using the independent samples t-test; within-group pre-post comparisons will employ the paired t-test. Non-normally distributed variables will be analyzed using non-parametric equivalents (Mann–Whitney U test or Wilcoxon signed-rank test). Multiple group comparisons will utilize one-way analysis of variance (ANOVA) with appropriate post-hoc correction (LSD or Bonferroni). Longitudinal data across repeated time points will be analyzed using repeated measures ANOVA or generalized estimating equations (GEE).(3) Multivariable analysis: to delineate the independent association between the IoT intervention and primary outcome measures (e.g., pulmonary function improvement, AECOPD frequency, readmission rate), multivariable logistic regression or Cox proportional hazards models will be employed, with adjustment for pre-specified potential confounders (including age, sex, comorbidities, and smoking history).(4) Missing data: missing data for key variables will be addressed using single and multiple imputation techniques to preserve sample integrity and maximize analytical efficiency.(5) Significance threshold: all statistical tests will be two-sided, with a significance level of *p* < 0.05. Where applicable, multiple testing corrections (e.g., Bonferroni correction) will be implemented to control the family-wise type I error rate.

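### The withdrawal rules end study participation, not just rehabilitation, for reasons that overlap the outcomes, which contradicts intention-to-treat

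*Protocol article*

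**What the plan says.** Section 2.2.3 (Study withdrawal criteria) opens with a mandatory rule: "Participants meeting any of the following criteria will be withdrawn from the study following enrollment". The listed criteria include:

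- "Development of a concurrent acute illness requiring intervention that would confound study outcomes"
- "Failure to complete required assessments, rendering evaluation of the primary outcome impossible"
- "Occurrence of a serious adverse event during follow-up that, in the investigator’s judgment, necessitates withdrawal from the trial"
- "Voluntary withdrawal, loss to follow-up, or death during the follow-up period"
- "Post-enrollment discovery that the participant does not fulfill any inclusion criterion or meets any exclusion criterion"

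The article does not distinguish stopping rehabilitation from stopping outcome follow-up, and nowhere says that withdrawn participants are still followed.

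The Abstract states: "Analyses will be performed on an intention-to-treat basis". It lists pneumonia incidence and all-cause mortality among the secondary outcomes. Section 3.1.1 defines the primary outcome as the number of moderate or severe exacerbations per patient over 12 months, taken from the hospital information system and confirmed by telephone. Section 3.1.2 records disease deterioration and unplanned healthcare use as adverse events. Item (4) of section 3.4 says that "missing data for key variables will be addressed using single and multiple imputation techniques". It does not mention withdrawn participants.

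**The concern.** Intention-to-treat needs two things: everyone is analysed in the allocated group, and outcome data are sought from everyone. A rule that ends study participation after enrolment works against the second, whatever the analysis section says.

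The difficulty is sharper here because several triggers are tied to what the study measures. A pneumonia is an acute illness that needs treatment, and it is also a secondary outcome. An admission for an exacerbation is a primary outcome event, and it can also be recorded as a serious adverse event. Death is a secondary outcome and a withdrawal criterion.

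The participants most likely to be withdrawn are therefore those with more events. If withdrawal is applied differently in the two groups, the comparison is distorted. If it is applied equally, information is lost. Enrolment requires a recent exacerbation history (section 2.2.1), so such events will not be rare.

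**Working it through.** **1. The rules set against the outcomes**

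| Trigger in 2.2.3 | Link to the outcomes | Effect |
|---|---|---|
| Concurrent acute illness | Pneumonia is a secondary outcome; exacerbation is not exempted | Can end follow-up because of an outcome event |
| Serious adverse event, by investigator judgement | Deterioration and unplanned care are recorded as adverse events | Same, at discretion |
| Death | All-cause mortality is a secondary outcome | An outcome is classed as a withdrawal |
| Late-found ineligibility | None | Departs from intention-to-treat, but is not outcome-driven |
| Incomplete assessments | Applies only if the primary outcome cannot be evaluated | Narrow, since records and calls supply that outcome |

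**2. The plan's own sample size**

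The 267 per group is reproduced by two proportions, 0.60 against 0.48 (risk ratio 0.80), two-sided 0.05, power 0.80, unpooled variance. Using 0.60 as the control risk is an inference.

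n = 7.849 × (0.60×0.40 + 0.48×0.52) / 0.12² = 7.849 × 0.4896 / 0.0144 = 266.9, so 267.

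Then 267 × 1.10 = 293.7, so 294. This point makes neither figure wrong.

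**3. Precision if withdrawn participants are dropped**

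Power = Φ[(0.12√n − 1.96√(2×0.54×0.46)) / √0.4896]

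| Share dropped from 294 | n per group | Power |
|---|---|---|
| 10% | 264.6 | 79.3% |
| 15% | 249.9 | 76.9% |
| 20% | 235.2 | 74.4% |
| 30% | 205.8 | 68.6% |

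**4. Possible bias (illustration only)**

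All inputs are assumed:

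- Control rate λ = 1.33 per year. Section 2.3 implies 0.3 to 1.8, that is 60% of 0.5 to 3.0.
- Gamma–Poisson counts with dispersion k = 0.5.
- 30% of events are severe.
- Each severe event leads to withdrawal with probability q.
- Withdrawn participants are dropped from the analysis.

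With p = 0.30 × q, the mean count among those who remain is λ(1 − p)/(1 + kλp), and the share leaving is 1 − (1 + kλp)^(−1/k).

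No true effect, q = 25% in A and 50% in B:

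- A: p = 0.075; mean 1.33×0.925/(1 + 0.665×0.075) = 1.2303/1.0499 = 1.172; 9.3% leave.
- B: p = 0.15; mean 1.33×0.85/(1 + 0.665×0.15) = 1.1305/1.0998 = 1.028; 17.3% leave.
- Rate ratio B/A = 1.028/1.172 = **0.88**. Reversed, it is 1.172/1.028 = **1.14**.

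Over the control rates implied by section 2.3:

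- λ = 0.3: 0.2494/0.2744 = 0.91, reversed 1.10.
- λ = 1.8: 1.348/1.560 = 0.86, reversed 1.16.

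Equal withdrawal, q = 25% in both groups: the null ratio stays at 1.00. A true 0.80 becomes 0.9464/1.1718 = 0.81.

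**5. The same withdrawals with person-time kept**

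Simulating the case in step 4 (25% against 50%, no true effect) and counting events over time to withdrawal gives a ratio of about 0.98 instead of 0.88. At 25% against 75% it gives about 0.96, against 0.77 when withdrawn participants are dropped. A correctly specified negative binomial model with a time offset removes nearly all of the remaining bias.

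**The case against.** The strongest reply is that section 2.2.3 does not say that withdrawn participants leave the analysis. The Abstract promises intention-to-treat, section 3.4 provides for imputation, and analysis sets are commonly defined in a fuller document that is not shown. This stands in part: a reader might infer that withdrawn participants will be deleted, but the text does not say so, and step 5 shows that most of the illustrated bias comes from deletion. It does not rescue the rule. Ending study participation stops data from arriving, and imputation does not replace follow-up that was stopped because of outcome-related events.

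Other stronger readings also fail:

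- **Every missed assessment triggers withdrawal.** The criterion requires that the primary outcome cannot be evaluated.
- **Every exacerbation or serious adverse event triggers withdrawal.** The first trigger needs a concurrent illness that would confound outcomes, most naturally something other than an exacerbation. The second needs the investigator's judgement. Overlap is a risk left open, not a stated consequence.
- **The bias favours the IoT group.** Closer monitoring in Group B makes events easier to notice, and the Discussion concedes that intervention providers are unblinded. But the article gives no withdrawal probabilities and does not say whether the deciding investigator is blinded.
- **The 10% attrition allowance is bound to fail.** Under the step 4 assumptions with a true ratio of 0.80, losing 26% to 31% requires every severe event to cause withdrawal. At 25% of severe events, this route removes about 9% of Group A.

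**Conclusion.** The contradiction stands. Section 2.2.3 states a mandatory, study-level withdrawal rule whose triggers partly overlap the primary and secondary outcomes. It cannot be reconciled with the Abstract's intention-to-treat statement, and it gives up outcome data that section 3.1.1 already has the means to collect. Late-found ineligibility breaks the same principle without being outcome-driven. Single imputation adds a smaller fault: it treats filled-in values as observed and so understates uncertainty.

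The size cannot be fixed from the documents. Under a dropped-participants analysis with the assumed inputs, unequal withdrawal moves a null rate ratio to about 0.88 or 1.14, against a planned effect of 0.80. Equal withdrawal causes little bias but reduces power, to about 74% if 20% are dropped. These figures show what is at stake if withdrawn participants are lost to the analysis; they do not predict this study's result.

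**What to change.** Reconcile the Abstract with sections 2.2.3, 3.1.1 and 3.4:

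- State that stopping the intervention does not end follow-up. The clinical rules for stopping it are left to the investigators.
- Follow every enrolled participant who has not withdrawn consent to week 52 for exacerbations, admissions and death, through the planned record review and calls.
- Analyse all of them in the allocated group, including those later found ineligible.
- Treat death as an outcome, with exposure time ending at death.
- Keep partial follow-up in the primary analysis through person-time.
- Delete single imputation, and use multiple imputation where imputation is needed.

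The cost is amendment wording, plus continued record review and calls for participants who stop the intervention. The sample size figures need not change on this account. The amendment should come before participants are withdrawn under the present rule, because follow-up lost that way may not be recoverable.

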### Sample size calculation

2.3

The primary outcome measure is the 12-month rate of moderate-to-severe AECOPD. Based on prior literature, the annual exacerbation frequency in patients with moderate-to-severe COPD ranges from 0.5 to 3.0 events, of which approximately 60% are classified as moderate or severe. Assuming a two-sided significance level (*α*) of 0.05 and a statistical power (1 − *β*) of 0.80, and informed by preliminary data and published evidence suggesting that PR interventions reduce exacerbation frequency by approximately 20% (risk ratio [RR] = 0.80), sample size calculations performed using PASS 2023 software indicated a requirement of 267 participants per group. Accounting for an estimated attrition rate of 10%, which is considered feasible given the chronic disease management context in the Shijiazhuang region, a 10% inflation factor was applied, yielding a final required sample size of 294 participants per group and a total sample of 588 participants.

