##### The primary outcome is the 12-month rate of moderate-to-severe AECOPD

3.1.1.1

Defined as the number of moderate or severe acute exacerbation events occurring per patient during the 12-month follow-up period. AECOPD is defined as an acute deterioration of respiratory symptoms (dyspnea, cough, and/or sputum production) requiring treatment with systemic corticosteroids and/or antibiotics, or necessitating hospitalization (10). Exacerbation data will be ascertained through review of the hospital information system and confirmed via structured telephone follow-up.

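### The 267 per group cannot be derived as an exacerbation-rate calculation from the stated inputs, so the 80% power is unsupported for the count primary outcome

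*Protocol article*

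**What the plan says.** Section 3.1.1.1 makes the primary outcome a count: "Defined as the number of moderate or severe acute exacerbation events occurring per patient during the 12-month follow-up period".

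Section 2.3 names the same outcome and gives these planning inputs:

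- An annual exacerbation frequency between 0.5 and 3.0 events, "of which approximately 60% are classified as moderate or severe".
- The error rates: "Assuming a two-sided significance level (*α*) of 0.05" and "a statistical power (1 − *β*) of 0.80".
- The effect, attributed to preliminary data and published evidence: "PR interventions reduce exacerbation frequency by approximately 20% (risk ratio [RR] = 0.80").

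The result is that "sample size calculations performed using PASS 2023 software indicated a requirement of 267 participants per group". For an expected 10% attrition, "a 10% inflation factor was applied, yielding a final required sample size of 294 participants per group and a total sample of 588 participants".

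The section gives no single control rate, no dispersion and no test.

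**The concern.** A sample size for a count outcome needs a control event rate, a measure of between-patient variability and a rate ratio. Section 2.3 offers a sixfold range for the rate and nothing for variability, yet arrives at one precise number.

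The 60% describes how exacerbation events split by severity. It does not say what proportion of patients has an event. Together with an effect labelled as a risk ratio, it has the form of the inputs to a two-proportion test. If it was used that way, the 80% power belongs to a binary endpoint that the trial does not have.

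The stated power is what readers will use to judge how informative a non-significant result is. If it does not belong to the primary outcome, they lack that guide.

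Two smaller matters sit in the same paragraph. The attrition allowance multiplies by 1.1 instead of dividing by 0.9. The 20% effect is described as that of PR, whereas both groups here receive a PR prescription (sections 2.5.1.2 and 2.5.2).

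**Working it through.** **Inputs from section 2.3:** two-sided alpha 0.05, power 0.80, ratio 0.80, equal groups, 0.5 to 3.0 exacerbations per year, 60% of them moderate or severe, 10% attrition. **Assumed here, not in the document:** negative binomial dispersion k of 0.5 and 1.0. Throughout, (1.960 + 0.842)² = 7.849.

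**1. Reproducing 267.** Treat 60% as a control-group patient risk, so the comparison is 0.60 with 0.60 × 0.80 = 0.48. The unpooled normal approximation gives

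n = 7.849 × (0.60 × 0.40 + 0.48 × 0.52) / 0.12² = 7.849 × 0.4896 / 0.0144 = 266.9, which rounds up to 267.

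Other versions of the same test give 270 (pooled), 270 (arcsine), 276 (log risk ratio) and 287 (continuity-corrected). The exact match is therefore specific to the unpooled formula.

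**2. The same inputs as a rate calculation.** The implied moderate-to-severe control rate r runs from 0.5 × 0.6 = 0.3 to 3.0 × 0.6 = 1.8 per year, with midpoint 1.05. For 12 months of follow-up,

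n = 7.849 × [1/r + 1/(0.8r) + 2k] / (ln 0.8)²,

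where (ln 0.8)² = 0.0498 and k = 0 is Poisson. With k = 0 this reduces to about 354.7 / r.

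Power at 267 per group is Φ(|ln 0.8| × √(267 / [2.25/r + 2k]) − 1.960).

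| Control rate per year | n per group, k = 0 | k = 0.5 | k = 1.0 | Power at 267, k = 0 | k = 0.5 | k = 1.0 |
|---|---|---|---|---|---|---|
| 0.3 | 1,183 | 1,340 | 1,498 | 27% | 24% | 22% |
| 1.05 | 338 | 496 | 654 | 70% | 54% | 43% |
| 1.8 | 198 | 355 | 513 | 90% | 68% | 53% |

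Neither end of the implied range nor its midpoint returns 267.

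**3. What a rate calculation would need in order to give 267.** Under Poisson, r = 354.7 / 267 = 1.33 per year. Under a negative binomial, 2.25/r + 2k must equal 1.694, for example r = 1.5 with k about 0.10, or r = 1.8 with k about 0.22. These values lie within the implied rate range, but the document states none of them.

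**4. Attrition.** 267 × 1.1 = 293.7, rounded up to 294. After 10% loss, 294 × 0.9 = 264.6, below 267. Dividing instead, 267 / 0.9 = 296.7, or 297 per group (594 in total). The shortfall is 3 enrolled per group. In the pooled two-proportion calculation, power is 79.6% at 267 and 79.3% at 265.

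**The case against.** The strongest reply is that the PASS output is not shown and the article names no test. A Poisson calculation at 1.33 per year also gives 267, and so do several negative binomial pairs. Section 2.2.1 requires at least two moderate exacerbations or one severe one in the preceding year, so a rate above the midpoint is plausible. The article is also condensed, and the planning rate and dispersion may stand in a fuller document.

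Much of this stands. A reader might infer that a two-proportion test has been shown to be the source of 267. It has not: the exact match is strong circumstantial evidence and no more. A reader might also infer that the trial is underpowered. The document does not establish that either, since at 1.8 per year without overdispersion power is 90%, and the overdispersed figures rest on assumed values of k.

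The reply does not rescue the paragraph as written. Section 2.3 does more than leave details out: it presents inputs and a result as one calculation. Read as a rate calculation, those inputs do not yield the result. Read as the calculation that does yield it, they use a share of events as a share of patients.

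On the effect size, a reader might infer that 0.80 is wrong for this contrast. That goes too far. The preliminary data cannot be seen, and the intervention adds device-based respiratory muscle training and prescribed walking to what the control group receives. What stands is that the text ties the 20% to PR and does not say that it is the effect expected over conventional PR.

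**Conclusion.** The point holds in this form: 267 per group does not follow as a rate calculation from the stated inputs, and the stated 80% power is unsupported for the count primary outcome. The coincidence with 60% versus 48% makes it likely, but not certain, that the share of events was used as a patient risk.

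At a rate ratio of 0.80, power at 267 per group lies anywhere from 27% to 90% over the implied rates under Poisson, and lower with overdispersion. Its direction relative to 80% is open because it turns on the unstated rate and dispersion. At the midpoint rate, however, it is below 80% even with no overdispersion. These figures assume a full 12 months of follow-up for every evaluable patient and an unadjusted comparison.

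The attrition step is wrong in method but small, at about 1% of the enrolment. It would not merit a separate point.

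**What to change.** Keep the planned enrolment of 588 and rewrite section 2.3 around the outcome that section 3.1.1.1 defines:

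- Use a negative binomial or other overdispersed rate calculation. State the control moderate-to-severe rate expected in this exacerbation-history population, the dispersion, the follow-up time and the rate ratio, with the basis for each.
- Stop using 60% as a patient risk. If it stays, use it only to convert an all-severity event rate into a moderate-to-severe rate.
- State explicitly that 0.80 is the assumed effect over conventional PR, and give the grounds for it.
- Report the power, or the detectable rate ratio, at about 265 evaluable per group (294 less 10%) over a small grid of control rate and dispersion. This also settles the attrition point without more patients. Holding to 267 evaluable would instead mean enrolling 297 per group.

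The cost is a re-run calculation and a rewritten paragraph. The downside is that the stated power may become less favourable than 80%.
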